### **8.2 Endpoints**

#### **8.2.1 Primary Endpoints**

The primary study objective is to evaluate the effectiveness and safety of a candidate vaginal microbicide, tenofovir gel, when applied intravaginally by women, in preventing sexually transmitted HIV infection. The primary endpoint of HIV infection will be assessed as described in Appendix III.

#### **8.2.2 Secondary endpoints**

Consistent with the study objectives listed in section 3.2, the following secondary endpoints will be assessed:

- deep epithelial disruption observed on pelvic examination

- pregnancy rates
- pregnancy outcomes, which will be assessed in the following categories: induced abortion; spontaneous abortion; stillbirth; live birth with a congenital anomaly; or live birth without a congenital anomaly.

For women who become infected with HIV during the trial, additional secondary endpoints will be assessed:

- viral load in the first available HIV positive blood specimen, and at 3 months after the first HIV positive specimen
- Tenofovir resistance assessed by resistance assay test performed on virus isolated from the first available HIV positive blood and genital specimen and 3 months after the first HIV positive specimen.
- Tenofovir resistance assessed by resistance assay test performed on virus isolated from participants testing HIV positive at the post trial assessment visit scheduled two months after study exit following product hold

### 8.2.3 Ancillary endpoint

Consistent with the ancillary objective listed in section 3.3, the following ancillary endpoints will be assessed

- The presence of STIs including HSV\_2 and HPV, diagnosed through retrospective analysis of stored samples, including but not limited to, antibody detection, viral nucleic acid and viral culture.

### 8.3 Accrual, follow-up, and sample size

The HIV incidence in the current longitudinal studies are 7.9 per 100 person years in the CAPRISA 002 study, 5.8 per 100 person years in the eThekweni CAPRISA 051 study and 7.3 per 100 person years in the Vulindlela CAPRISA 050 study. We assume that the infection rate will be slightly lower than this in the placebo arm of the study, and have therefore assumed an incidence rate of 7 per 100 person years as the rate in the placebo group.

We plan to enrol up to 1250 women over approximately 18 months and to continue follow-up until 92 incident infections are observed (unless the DSMB recommends discontinuing the trial early, see section 7.4). This number of events is expected to provide 90% power to detect a 50% effect (using a two-sided  $\alpha=0.05$  significance level test). Assuming an HIV incidence rate of 7 per 100 person years and 10% annual loss to follow-up, the required number of incident infections (92) will be reached approximately 12 months after the end of the enrolment period, resulting in a total study duration of approximately 30 months. Sample size and power were calculated using NQUERY.

The chance of detecting various other levels of effectiveness levels ranging from 30% to 60% at the two-sided,  $\alpha=0.05$  significance level are provided in Table 6.

**Table 6:** Power to Detect Different Levels of Product Effectiveness at the Two-Sided  $\alpha = 0.05$  Significance Level Assuming 68 Events are Observed

| Actual product effectiveness (reduction in risk for active gel relative to placebo gel) | Power to detect an effect ( $p < 0.05$ ) |
|-----------------------------------------------------------------------------------------|------------------------------------------|
| 60%                                                                                     | 97%                                      |
| 50%                                                                                     | 90%                                      |
| 40%                                                                                     | 74%                                      |
| 30%                                                                                     | 41%                                      |

The power to detect an effect of tenofovir gel on the first secondary safety objective, the rate of deep epithelial disruptions, is provided in Table 7.

**Table 7:** Power to Detect Differences in Deep Epithelial Disruption Rates (Assumes Two-Sided Alpha of 0.05, 10% Annual Loss to Follow-up, 18 months of Recruitment and Total Study Duration of 30 Months, Sample Size of up to 1250)

| Baseline Rate
(per 100 person years in placebo group) | Power to Detect a: |                 |                 |
|----------------------------------------------------------|--------------------|-----------------|-----------------|
|                                                          | 2-fold increase    | 3-fold increase | 4-fold increase |
| 1                                                        | 45%         | 80%      | >99%  |
| 2.5                                                      | 83%         | >99%            | >99%            |
| 5                                                        | 98%         | >99%            | >99%            |

The sample size will be re-assessed approximately 2 months before the expected enrolment of the last participant, based on the observed event rate pooled across treatment arms. If it is determined at this time that additional participants will likely be required to yield the required number of incident HIV events (i.e.92) by the end of 30 months of follow-up, then consideration will be given to enrolling additional women, up to a maximum of 1500 women.

The Principal Investigators and protocol statisticians will periodically review the overall product adherence and HIV infection rate data (pooled across treatment arms) to determine if any protocol changes with respect to duration of follow-up should be implemented. For example, if recruitment rates are lower than expected and overall adherence or infection rates decrease with longer study participation, then the protocol may be amended to limit the maximum number of months of follow-up for participants.

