### **3.4.3 Enrolment and Randomisation**

As described more fully in section 4.4, potential study participants will be screened for eligibility and eligible participants will be enrolled in the study within 30 days of screening. At each of the two sites, eligible participants who provide informed consent to take part in the trial will be assigned randomly to either tenofovir gel, or placebo gel in a 1:1 ratio.

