#### **7.4 Data, Safety, Monitoring Board**

An independent Data Safety Monitoring Board will be assembled for this study. The details for the operation and responsibilities of the DSMB will be defined in a separate DSMB Operational Plan, which will be included in the MOP. The Operational Plan will delineate the composition, duties, responsibilities and procedures of the DSMB, data required at each meeting as well as the analyses that will be conducted, i.e. interim comparisons of the efficacy and safety of the study products.

Interim monitoring reports will be generated by an independent statistician (who is not otherwise involved in the study) and submitted to the DSMB (some data that go to the DSMB will be “open” and available to the study team, like grouped data listed below). All reports created by the independent statistician will be distributed to the members of the DSMB only and will not be available to any study staff. DSMB reports will be kept in a locked file with restricted access.

A full interim review of the available data will be undertaken during the conduct of the study. These interim reviews will be triggered once 22 of the anticipated primary endpoints are reached and again once 68 of the anticipated primary endpoints are reached. The data to be reviewed will include:

- Accrual data
- Baseline data
- Retention data
- Safety data
- Quality assurance data
- Effectiveness data (The type I error rate will be controlled over the two planned interim analyses plus the final analysis using O’Brien-Fleming type boundaries with the Lan-Demets spending function.)
- Any other data requested by the DSMB

After each DSMB meeting, the Chairperson will issue a written report describing all recommendations. The DSMB could recommend that the study should proceed as designed, should proceed with design modifications, or should be discontinued due to any reason (safety, efficacy, futility, etc.).

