## 8.6 Data Analysis

An expanded Statistical Analysis Plan (SAP), covering both the final analysis and the planned interim analysis, will be finalised before the first participant is enrolled. The following is a summary of the planned analyses. Any deviations to be made from this summary plan will be documented in the detailed SAP.

All primary analyses will be performed on an intention to treat (ITT) basis. For the ITT analysis, patients will be analysed according to the treatment arm they were randomised to, even if the participant was off product or received the product they were not assigned for a period of time while in the study. The only participants excluded from this primary analysis population will be women without a post-randomisation HIV test result, and women whose stored baseline blood samples were later found to be HIV positive. All primary and secondary analyses will be two-sided and will be performed at the 0.05 level of significance (adjusted to account for the two planned interim analyses). Additional analyses could be performed on other study populations, for example an as treated or a per protocol population. These analyses will be described in the SAP.

Any key decisions regarding the timing of outcomes, the appropriateness of test statistics or model assumptions, the eligibility of participants to be included in the various populations or any other statistical issues will be made in a blind review meeting. At the blind review at least the following people will be present: protocol statisticians; Principal Investigators; medical officer; and data manager. Only after this group documents that all data are sufficiently clean and all decisions regarding individual participant outcomes have been made will the study be unblinded to the true randomisation assignments

To assess effectiveness and safety of tenofovir gel the cumulative probability of HIV will be calculated for each treatment group using the Kaplan-Meier method. The difference in survival curves will primarily be evaluated with a logrank test, stratified by site. The type I error rate will be controlled over the two planned interim analyses, as well as the final analysis, using O'Brien-Fleming type boundaries with the Lan-Demets spending function. Secondly, proportional hazards regression models will be used to estimate the hazard rate ratio, along with a 95% confidence interval, controlling for site and selected baseline prognostic variables (to be identified in the SAP).

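### Table 6 states power for 68 events although the trial is sized on 92, and its 40%-effect row is 5 to 7 points too high even at 92 events

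*Protocol*

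**What the plan says.** Protocol section 8.3 plans "to continue follow-up until 92 incident infections are observed" and adds: "This number of events is expected to provide 90% power to detect a 50% effect", at two-sided 0.05. The 92-event target also appears in the Schema and in sections 3.4.2 and 8.1.

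Table 6, in the same section, is offered as the power for a range of effects. Its heading ends "Significance Level Assuming 68 Events are Observed". Its rows are 97% power for a 60% reduction in risk, 90% for 50%, 74% for 40% and 41% for 30%.

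Outside that heading, 68 appears only in section 7.4, where interim reviews are triggered at 22 endpoints and "again once 68 of the anticipated primary endpoints are reached".

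**The concern.** Power for an event-driven log-rank comparison depends on the number of events. Section 8.3 therefore cannot attach the same 90%, for the same 50% effect and the same significance level, to both 92 and 68 events.

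Two readings could mislead:

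- **Power below the design effect.** Table 6 is the protocol's only statement of what the trial can detect if the gel is less than 50% effective. At a 40% effect it implies a 26% chance of missing a real benefit.
- **Power at 68 events.** Because 68 is a real review point, the heading can be read as saying that 90% power is already available there. Section 7.4 lets the DSMB recommend discontinuation for efficacy or futility. Section 3.4.2 asks for its advice on futility if 92 events are not reached within 30 months.

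**Working it through.** **Inputs from the protocol**

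- Events: 92 (section 8.3 text) or 68 (Table 6 heading).
- Test: "The difference in survival curves will primarily be evaluated with a logrank test, stratified by site" (section 8.6).
- Level: two-sided 0.05 (sections 8.3 and 8.6), so z = 1.96.
- Allocation: 1:1 (section 3.4.3).
- Effects of 60, 50, 40 and 30% are taken as hazard ratios (HR) of 0.4, 0.5, 0.6 and 0.7.

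**Formulas**, with d events and Φ the standard normal distribution function

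- Schoenfeld: power = Φ(½·√d·|ln HR| − 1.96)
- Freedman: power = Φ(√d·(1 − HR)/(1 + HR) − 1.96)

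**Step 1: the main sizing.** For HR 0.5 and 90% power, (1.960 + 1.282)² = 10.507.

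- Schoenfeld: 4 × 10.507 / 0.6931² = 87.5, so 88 events.
- Freedman: 10.507 × (1.5/0.5)² = 94.6, so 95 events.
- At 92 events (√92 = 9.592), Schoenfeld gives Φ(3.324 − 1.96) = 91.4% and Freedman Φ(3.197 − 1.96) = 89.2%.

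The 92-event, 90%-power statement reproduces.

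**Step 2: Table 6 at 68 and at 92 events** (Schoenfeld / Freedman)

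| Effect | Table 6 | 68 events | 92 events |
|---|---|---|---|
| 60% | 97% | 96.5 / 94.2% | 99.3 / 98.4% |
| 50% | 90% | 81.5 / 78.5% | 91.4 / 89.2% |
| 40% | 74% | 55.8 / 54.0% | 68.8 / 66.9% |
| 30% | 41% | 31.2 / 30.7% | 40.2 / 39.5% |

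For example, at a 40% effect and 92 events, Schoenfeld is Φ(½ × 9.592 × 0.5108 − 1.96) = Φ(0.490) = 68.8%. Freedman is Φ(9.592 × 0.25 − 1.96) = Φ(0.438) = 66.9%.

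- **As headed (68 events):** the 50% row is too high by 8.5 to 11.5 points, the 40% row by 18 to 20, and the 30% row by about 10.
- **With the heading changed to 92:** the 40% row is still too high by 74 − 68.8 = 5.2 to 74 − 66.9 = 7.1 points. The 60% row is slightly low, and the 50% and 30% rows are within 2 points.
- An exact conditional binomial calculation at 92 events gives 98.9, 90.0, 66.9 and 38.7%, the same picture.

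**Step 3: event count implied by each row.** Each formula is solved for d at the printed power. The ranges allow for rounding of ±0.5 point.

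| Effect | Schoenfeld | Freedman |
|---|---|---|
| 60%, power 97% | 70 (68–73) | 80 (78–84) |
| 50%, power 90% | 88 (86–89) | 95 (93–96) |
| 40%, power 74% | 104 (103–105) | 108 (107–110) |
| 30%, power 41% | 94 (93–96) | 96 (95–98) |

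Under Schoenfeld no two ranges overlap. Under Freedman only the 50% and 30% rows do. A search over 40 to 159 events found no count that puts all four rows within 2 points, by either formula (one- or two-sided), exact or approximate binomial, or a Wald test of the rate ratio. The closest was two-sided Freedman at 103 events (99.2, 92.3, 71.8 and 43.3%), with a largest miss of 2.3 points.

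**Step 4: a calendar-driven calculation.** The section 8.3 assumptions are 1250 women, 18-month accrual, 30 months in total, 7 infections per 100 person-years on placebo and 10% annual loss. If events are allowed to vary with the effect, a 40% effect yields about 106 events and 73 to 75% power, close to the stated 74%. The same inputs give about 112 events and 46 to 47% power at a 30% effect, against the stated 41%. None of the sample sizes tried, from 980 to 1500, brought both rows within 2 points.

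**The case against.** The best defence is that little depends on Table 6. The 92-event target is sound and repeated consistently, and the sample-size re-assessment in section 8.3 uses 92. The test, the significance level and the end of follow-up do not refer to the table. If the heading read 92, three of the four rows would stand within about 2 points. What remains is one wrong number in a heading and one cell 5 to 7 points too high. That is a fair description of the extent of the error, and the correction is correspondingly small.

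Three further points limit what can be claimed:

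- **Cause.** The protocol says nQuery was used but gives neither module nor inputs. Working back from rounded percentages shows that the rows do not agree with one another; it does not show how they arose. The 74% may come from a calendar-driven calculation, but that does not rescue the table, because it fails at the 30% row and the trial stops on events.
- **Tolerance.** Whether a single event count fits depends on how much error is allowed. At 2.3 points, 103 events would pass, but 103 is neither of the protocol's numbers.
- **DSMB misreading.** This is a possibility, not a certainty. The table's power column is labelled p < 0.05, and sections 7.4 and 8.6 place the interim looks under O'Brien-Fleming type boundaries. The protocol also does not rank effect sizes, so the point does not rest on 40% being more likely than any other value.

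**Conclusion.** The concern holds. The 68 in the Table 6 heading contradicts the 92-event sizing. As headed, three of the four rows overstate power by about 8 to 20 points. At 92 events the 40% row remains overstated by 5 to 7 points: the chance of missing a true 40% effect is about 31 to 33%, not 26%.

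The result assumes proportional hazards, 1:1 allocation and an unadjusted two-sided 0.05 level. Allowing for the interim looks would lower power slightly, so it cannot explain the 74%.

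The 92-event target is not in question. The table must still be corrected, because it misstates power for the primary endpoint and names an event count at which the DSMB will review effectiveness. At 68 events, power for a 50% effect is about 79 to 82% at unadjusted 0.05, and lower at the interim boundary.

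**What to change.** Head Table 6 with 92 events and recompute all rows by one method, named in the text. Expected values are about 98 to 99% (60% effect), 89 to 91% (50%), 67 to 69% (40%) and 40% (30%). State whether the figures use the unadjusted 0.05 or the final-analysis level after interim spending.

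If power at the second interim look is wanted, show it separately at its own boundary. At 68/92 = 74% of the information, the cumulative two-sided O'Brien-Fleming type spend is about 0.018 or 0.023, depending on whether the spending function is applied per side or two-sided. This addition is optional and could sit in the SAP.

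The cost is one table correction at the next protocol version. Sample size, event target and analysis do not change; the stated power at a 40% effect becomes less favourable.

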#### 8.4 Random Assignment and allocation concealment

A randomisation plan describing procedures for randomisation, allocation concealment, and blinding will be established prior to initiating the trial. A summary of the procedures is as follows: Enrolled participants will be assigned at random to one of the two study treatment arms in equal proportions. However, to facilitate blinding without greatly complicating product distribution logistics, each participant will be randomly assigned on one of six different groups (designated by an alphanumeric variable e.g., A, B, C, D, E and F) in a 1:1:1:1:1:1 allocation ratio. Three groups will correspond to the placebo gel and three to tenofovir gel.

The randomisation statistician, who is not otherwise involved in the study will randomly assign three of the alphanumeric variables to placebo and three to the active gel. This information will be sent to CONRAD for drug packaging and will be stored in a locked file cabinet (paper copy) and in a secured computer directory (electronic copy) at the CONRAD office. Except for key individuals involved in drug packaging, the treatment code (e.g., which 3 alphanumeric variables correspond to active drug and which 3 correspond to placebo) will not be known to anyone else. These treatment codes may only be revealed to the DSMB for planned interim analyses. Individual treatment assignments may also be revealed to the study investigators in the event that emergency unblinding of a study participant is required (see Section 8.5 for details). Any instances of unblinding, intentional or otherwise, will be documented in the study files. .

The randomisation list used to assign individual study participants to one of the six groups will be generated by a randomisation statistician who is not otherwise involved in the study. This statistician will use a randomly permuted block design, stratified by site. Two or more pre-specified block sizes will be recorded on a formal randomisation request form, but they will not be written in the protocol or communicated to the clinical staff in order to reduce the chance of the clinical staff anticipating the assignment of the next subject. Electronic copies of the randomisation schedule and the programs used to generate the randomisation schedule will be limited in access and password protected. Paper copies of the randomisation schedule will be locked in a secure location at the CAPRISA office, where no unauthorized study staff will have access to them.

The randomisation statistician will provide the study pharmacy at each site with sealed, opaque randomisation envelopes, sequentially labelled by participant identification number (PID). These envelopes will be assigned in sequential order to eligible study participants. Upon opening the envelope the pharmacist will add his or her name and signature as well as the time and date the envelope was opened. The treatment letter to which the participant was assigned will be known only to the pharmacist.

## 8.5 Blinding

Both study staff and participants will be blinded to treatment assignments. Blinding will be maintained until all data are entered into the study database, all primary study endpoint data have been cleaned and verified, preliminary analyses have been performed, and the data are ready for final analysis. If study data that are not part of the primary or secondary outcomes are still outstanding at the time of the proposed locking of the database, the database could be locked, and participants treatment assignments revealed, provided that the study statisticians and Principal Investigators agree that these data are not needed to perform the primary or secondary analyses. If necessary, the DSMB Chair may be asked to consider and make a determination on this request.

It is not anticipated that unblinding will be necessary for the provision of medical treatment or to otherwise protect the safety of study participants. In the event that an Investigator is concerned that a participant might be put at undue risk by continuing product use, the Principal Investigators or designee may discontinue product use by this participant, without knowledge of the actual treatment assignment. However, in the unlikely event that a study staff member feels that specific product knowledge is necessary to protect a participant's safety, he/she will notify the Principal Investigators and the protocol statisticians to consider and jointly rule upon the request. The DSMB Chair may also be asked to consider and make a determination on this request. If deemed necessary, then the procedures outlined in the randomisation, allocation concealment and unblinding plan will be followed for requesting and documenting unblinding of individual study participants.

All study participants will be administered a brief unblinding assessment at their study exit visits in which they will be asked to report which study product they think they received. A sample of study staff will complete a similar assessment after the close of each study site.

